**Outcomes for TND study of symptomatic GP visit**

TND requires both confirmed test positive cases and test negative controls to be identified. Both positive cases and negative controls should present to their GP with a defined set of symptoms, consistent with those required for participation in the sentinel swabbing scheme. Swabbing should be undertaken within ten days of onset of symptoms. Indications for swabbing include influenza-like illness, COVID19-like illness, acute respiratory infection, and asthma/COPD exacerbations.

A case is defined as an individual with a positive SARS-CoV-2 test via the sentinel swabbing scheme, with symptoms/illness within 10 days of onset.

A control is defined as an individual with a negative SARS-CoV-2 test via the sentinel swabbing scheme, with symptoms/illness within 10 days of onset AND (Autumn boosters only) influenza negative.

Multiple results may be available within any one individual, but a 90-day window between consecutive positive tests will be included in either study to ensure independence of positive outcomes.

Once timing of positive events have been established for the TND, the first negative result per 3 week period will be included, if at least 21 days before or 90 days after any positive result.

Analyses will initially exclude individuals presenting with asthma/COPD exacerbation, but indications for swabbing will be further explored in sensitivity analyses.

**3.7 Sub-groups**

Study subjects may be categorised according to age groups and Department of Health defined risk categories for COVID-19 vaccination.^[[6]](#footnote-6)^ The clinically high-risk groups include:

- chronic respiratory disease, including chronic obstructive pulmonary disease (COPD) and cystic fibrosis
- severe asthma
- chronic heart disease (and vascular disease)
- chronic kidney disease
- chronic liver disease
- chronic neurological disease including epilepsy
- diabetes
- immunosuppression due to disease or treatment, including solid organ, bone marrow and stem cell transplant recipients and people with specific cancers
- asplenia and splenic dysfunction
- morbid obesity
- severe and profound learning disability
- severe mental illness

Some clinical risk groups may be suitable to break down further, if required:

- chronic kidney disease, by severity
  - latest recorded stage 3 and latest GFR ≥ 30 and no record of dialysis
  - latest recorded stage 4-5 or latest GFR < 30 or record of dialysis
- diabetes, by type
  - type 1
  - type 2
- immunosuppressed
  - Conditions that compromise bone marrow function
  - Solid organ transplants
  - Immunosuppressive treatments
  - Cancer treatments
  - Primary and acquired immunodeficiencies

Definition and identification of risk groups:

| High risk is determined by age group and the presence of recognised risk morbidities recorded in the electronic health record for the patient concerned.  Pre-defined SNOMED codes have been established for these various underlying risk factors (rather than by questionnaire). We are in the process of establishing a formal agreement with Nottingham University PRIMIS to use the SNOMED CT codes that they have developed for these various underlying risk factors. In return for using these we have been asked simply to acknowledge the work done by Nottingham University in developing these clinical terms lists . |
| --- |

**3.8 Confounding factors and effect modifiers**

To control for differences in health status in vaccinated individuals compared with non-vaccinated, information on potential confounding factors is collected.

***Presence of chronic disease*** (according to Nottingham University PRIMIS specification)

- Major chronic disease groups identified in Section 3.7

**Propensity to consult**

- Number of consultations per patient for outcomes in previous year (e.g. Sep 2021-Aug 2022)
- Will be used to create age-standardised quartiles of consultation and a non-consulters group

**Indicators of co-morbidity and underlying ill health**

- Cambridge Mortality Measure (in age-standardised quartiles/quintiles).
- Smoking.
- Electronic Frailty Index

**Demographic**

- Age (on 31st August 2022, in 5 year bands up to age 89, then 90+),
- Sex,
- Ethnicity (in 5 broad groups)

**Deprivation**

- At patient level the standard English Index of Multiple Deprivation (IMD 2019) will be used in quintiles,
- at practice level if unknown at patient level.

**Location (Practice/ region)**

- If possible a factor for practice will be included in the analysis. This may prove difficult analytically, in which case NHS region will be used.

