**3.2 Study population and data source**

| Study population to be included:  Cohort study: Approx. 18,800,000 registered persons in England. About 20% of the study population are ≥65 years.  Swab based TND study: Restricting to those consulting their GP with symptoms and swabbed via the sentinel scheme, available positive cases and negative controls will depend on current prevalence and swab rates.  Spring 2023 boosters, will restrict to: individuals aged 75+, immunosuppressed individuals aged 16+  Autumn 2022/2023 boosters, will restrict to: individuals aged 50-74, individuals aged 75+, individuals aged 16+ in clinical risk groups |
| --- |

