**3.3 Study setting**

| **Cohort**  Total number of practices: ~1800,  Size of population: ~18,800,000 registered persons (all patients registered in the practices).  Representativeness: The population is closely representative of the English national population by region and by age and gender. The population is about one third of the national population.  For practical purposes this is a complete database of information collected in the sentinel networks. Given the programme of enhanced data extraction which is underway we would not expect to lose more than 2% of relevant data.  The practice data bases are an accumulated record of person-specific health-related data. We extract selected data to provide our routine surveillance program. |
| --- |

| ***TND***  Participants in the RCGP/UKHSA sentinel swabbing scheme. These are patients who contacted their GP, where the GP was part of the Royal College of General Practioners Research and Surveillance Centre (RCGP-RSC) sentinel scheme, and who had a sentinel respiratory swab taken with a result for SARS-CoV-2. >200 practices contribute sentinel swabs for virology.  Indications for swabbing are influenza-like illness, COVID19-like illness, an acute respiratory infection or exacerbation of asthma/COPD with onset within the last 10 days.  Patients are either swabbed and consented by their GP as part of a face-to-face consultation, or directed to take a postal self-swab by GPs through takeatestuk.com after being issued a voucher code.  All sentinel swabs are tested for respiratory infections including influenza and RSV using RT-PCR at UKHSA’s Virus Reference Laboratory. Vaccination data are available via linkage to GP records. |
| --- |

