**TNCC**

The plots below show the bottom end of the 95% CI around a VE of 60% and 90% when there are 4 controls per case (i.e. for TNCC 20% are positive and 80% negative) for various coverage figures. (~20% positivity November 2020)

A: 60% VE

[figure not shown]

B: 90% VE

[figure not shown]

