**TND study**

V/E is calculated as 1-OR. Where OR is the odds of vaccination in cases compared to controls (SARS-CoV-2 negative).

Multivariable logistic regression will be used with adjustment for week of swab, age group, risk-status and region (or practice), at minimum. Inclusion of additional variables including sex, consultation quartile, ethnicity, IMD quintile, smoking status, EFI, large residence, Cambridge Morality Measure, and indication for swabbing (grouped as ILI / COVID-like illness, ARI or exacerbation) will be considered individually; variables that do not impact VE by more than 1% need not be included.

Vaccination status will be a categorical variable, captured at the time of swabbing: 0-13 days post dose, 14-91 days post dose, 92-182 days post dose, with separate categories for each vaccine type (or manufacturer if required). Vaccinated 6months+ ago will be the baseline category, to look at the incremental benefit of a new dose.

Primary TND analysis will impute onset status (within/beyond 10 days) where this is not given.

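### A fixed practice factor in the COVID-19 TND's ordinary logistic regression overstates VE if swabs per practice are few

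*Protocol*

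**What the plan says.** Section 3.8 (Location), which serves both designs, ranks practice ahead of region: "If possible a factor for practice will be included in the analysis". It then gives the fallback: "This may prove difficult analytically, in which case NHS region will be used".

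Section 3.12 (TND study) fixes the model: "Multivariable logistic regression will be used with adjustment for week of swab, age group, risk-status and region (or practice), at minimum". No conditional, mixed or penalised fit is named. The effect measure is stated as "V/E is calculated as 1-OR".

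Section 3.3 says that ">200 practices contribute sentinel swabs for virology". No section gives the number of swabs, in total or per practice. Section 3.2 says only that "available positive cases and negative controls will depend on current prevalence and swab rates".

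Several provisions thin the data:
- Section 3.2: "Spring 2023 boosters, will restrict to: individuals aged 75+, immunosuppressed individuals aged 16" and over.
- Section 2.2 makes VE by clinical risk group and by time period primary questions.
- Section 3.4 plans to split Autumn 2022 by dominant variant.
- Section 3.12 (All studies) allows stratification by age, risk group or variant period.

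**The concern.** A practice factor in ordinary logistic regression estimates a separate intercept for each of 200 or more practices alongside the vaccine effect. When each intercept rests on few swabs, the estimated log odds ratio is inflated in absolute size (the incidental-parameter problem). Because VE is one minus the odds ratio, an effective vaccine looks better than it is. Practices whose swabs are all positive or all negative contribute nothing.

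The protocol's safeguard is a move to region if the practice model is hard to fit. A sparse model of this kind can converge normally, and no rule ties the choice between practice and region to the number of swabs per practice. The exposure is greatest in the narrow groups where the protocol wants specific answers: the Spring population, single risk groups and variant periods.

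**Working it through.** **Is there a figure to reproduce?** The protocol states no TND sample size or swab count, and its precision plots are not shown. The one checkable TND input agrees with itself: four controls per case gives 1/(1+4) = 20% positive (Section 3.10, TNCC).

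**Inputs from the protocol:** more than 200 practices (200 used); 20% positivity; VE = 1 - OR; VE of 60%, one of the two values used in Section 3.10. VE of 40% was added as a lower case.

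**Assumptions:** swabs per practice m from 5 to 100, Poisson distributed; vaccine coverage 50%; between-practice SD of 0.3 on the logit scale.

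**Rough hand check.** With m swabs per practice, fixed practice intercepts inflate the log odds ratio by roughly m/(m-1), so the expected estimate is VE = 1 - OR^(m/(m-1)).
- True OR 0.40: m = 5 gives 1 - 0.40^1.25 = 68.2%; m = 10 gives 63.9%; m = 20 gives 61.9%; m = 50 gives 60.7%.
- True OR 0.60: 47.2%, 43.3%, 41.6% and 40.6%.

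**Simulation** (median of 120 to 300 replicates per cell; both models fitted to the same data):

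| Swabs per practice | True VE 60%: practice factor | True VE 60%: conditional | True VE 40%: practice factor | True VE 40%: conditional | Swabs in practices with both results |
|---|---|---|---|---|---|
| 5 | 68.3% | 60.6% | 46.8% | 40.2% | 70% |
| 10 | 64.1% | 60.2% | 42.7% | 39.6% | 88% |
| 20 | 62.2% | 60.3% | 41.4% | 39.8% | 98% |
| 50 | 60.9% | 60.2% | 40.3% | 39.7% | 100% |
| 100 | 60.5% | 60.2% | 40.5% | 40.2% | 100% |

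A separate simulation with 200 practices gave about 69%, 65%, 62% and 61% at 5, 10, 20 and 50 swabs for true VE 60%, and about 45%, 43%, 41% and 41% for true VE 40%. Taking both together, the excess at 5, 10, 20 and 50 swabs is about 8 to 9, 4 to 5, 2 and 1 points for true VE 60%. For true VE 40% it is about 5 to 7, 3, 1 and at most about 1.

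**Sensitivity, true VE 60%:**
- At 10% positivity the practice factor gives 67.8%, 63.6% and 61.3% at 5, 10 and 20 swabs. At 30% it gives 68.6%, 63.8% and 61.7%.
- Very uneven practice sizes (negative binomial, k = 0.5; 40 replicates) reduce the excess: 65.2%, 62.1%, 61.5% and 60.9% at means of 5, 10, 20 and 50.
- A region factor (seven levels assumed) with the same total swabs gives 59.5% to 61.0%.
- With true VE of zero there is no systematic bias.

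**Scale.** With 200 practices, 50 swabs each means 200 × 50 = 10,000 eligible swabs in the analysed stratum; 20 each means 4,000.

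**The case against.** A reader might infer that the TND estimate will be biased upward. The documents do not support that. No section gives swabs per practice, region is a named alternative in both places, and the protocol does not spell out dummy variables: conditional and mixed models are also logistic regressions, and the estimator could be left to an SAP. This stands, and it makes the point conditional. A plain factor in ordinary logistic regression is nevertheless the natural reading of the text.

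The fallback may work better than feared. At 5 swabs per practice about 30% of swabs fall in single-result practices, and an analyst may well call that a difficulty and move to region. This also stands in part. The signal fades faster than the bias, however: at 10 swabs about 12% are lost with 4 to 5 points of excess, and at 20 about 2% are lost with 2 points (true VE 60%).

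The bias sits inside sampling error in sparse strata: at 6 swabs per practice and true VE 40%, the SD of the estimated VE is about 11 points. Section 4.3 already warns of wide intervals. But a wide interval centred in the wrong place is a different defect, and this one has a consistent direction.

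It is tempting to say that the excess breaches the protocol's 1% criterion. In Section 3.12 that criterion decides whether additional covariates enter the model. It is not a tolerance for bias, and location is already in the minimum set.

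Nor does the loss of single-result practices count against the practice factor alone, since conditional logistic regression discards the same practices.

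**Conclusion.** The point holds as a conditional one. If practice is fitted as a fixed factor in the TND's ordinary logistic regression and swabs per practice are few, VE for an effective vaccine is overstated. The excess is several points at 5 to 10 swabs per practice, about 1 to 2 points at 20, and about 1 or less from 50 upward. These sizes rest on assumed swab numbers, 200 practices, about 20% positivity and true VE of 40% or 60%. They shrink when practice sizes are very uneven and vanish when the vaccine has no effect.

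Large all-population analyses may be unaffected. The risk lies in the restricted and stratified ones, where the stated fallback does not reliably prevent it. The Poisson cohort model does not share this bias.

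**What to change.** State in Section 3.8 (Location) and Section 3.12 (TND study) that, in the TND, practice is adjusted for by conditional logistic regression grouped on practice. Otherwise NHS region is used, for example when swabs per practice are few and the loss of single-result practices is material. Add that unconditional practice dummies are not used in sparse strata. The cohort text can stay as it is.

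The cost is one sentence, a different Stata command and slightly wider intervals. Single-result practices will still contribute nothing.

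A random intercept for practice is a possible alternative, but it was not tested here. It assumes practice effects unrelated to vaccination, which weakens the confounding control that a practice factor is meant to give.

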**Time/circulation**

- Week, using smoothing splines.
- Interaction with week and NHS regions, and week and age groups will be checked and the model with the lowest AIC (Akaikes’ information criterion)

**Influenza vaccination**

**Resident in a large household**

- Via household key. Single occupancy and large communal establishments have consistently been associated with test positivity and risk of mortality.^[[7]](#footnote-7)^,^[[8]](#footnote-8)^,^[[9]](#footnote-9)^
- We assign to groups based on median age <70, 70+ (e.g. care homes).

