**Table 1: Data sources for each collected variable**

| Group of Variables | Variables | Data source |
| --- | --- | --- |
| Demographic characteristics | Age on 31 August 2022 | Electronic GP record |
|  | Gender | Electronic GP record |
|  | GP practice ID | Electronic GP record |
|  | Location – NHS region | Electronic GP record |
|  | IMD quintile | Electronic GP record |
|  | Ethnicity | Electronic GP record |
| Exposure | COVID-19 vaccinations | Electronic GP record / linkage to NIMS |
|  | Dates of vaccinations | Electronic GP record / linkage to NIMS |
|  | Type of vaccine / manufacturer | Electronic GP record / linkage to NIMS |
|  | Batch numbers | Electronic GP record / linkage to NIMS |
| Outcomes TND only | Laboratory confirmed outcome | Linkage to PHE virus reference lab data |
|  | Date of swab | Linkage to PHE virus reference lab data |
|  | Date of onset | Linkage to PHE virus reference lab data |
|  | Date of receipt | Linkage to PHE virus reference lab data |
|  | Presence of fever ±10d | Electronic GP record |
|  | Presence of cough ±10d | Electronic GP record |
|  | Presence of shortness of breath ±10d | Electronic GP record |
|  | Consultation for ILI ±10d | Electronic GP record |
|  | Consultation for COVID19 ±10d | Electronic GP record |
|  | Consultation for URTI ±10d | Electronic GP record |
|  | Consultation for LRTI ±10d | Electronic GP record |
|  | Consultation for ARI ±10d | Electronic GP record |
|  | Consultation for Bronchitis ±10d | Electronic GP record |
|  | Consultation for Bronchiolitis ±10d | Electronic GP record |
|  | Consultation for asthma/COPD ±10d | Electronic GP record |
| Outcomes cohort only | Date of hospital admission | Linkage to HES / SUS data |
|  | Date of discharge | Linkage to HES / SUS data |
|  | List of ICD10 discharge codes | Linkage to HES / SUS data |
|  | Use of Oxygen | Linkage to HES / SUS data |
|  | Date of ICU admission | Linkage to HES / SUS data |
|  | Date of Death | Electronic GP record / linkage to ONS mortality data |
|  | Date of positive SARS-CoV-2 test | Linkage to SGSS / PHE virus reference lab data |
| Confounding factors | Smoking status | Electronic GP record |
|  | List of PRIMIS risk groups | Electronic GP record |
|  | Electronic Frailty Index | Electronic GP record |
|  | Indicator of living in a large residence | Electronic GP record (household key) |
|  | Cambridge Mortality Measure | Electronic GP record |
|  | Consultation count | Electronic GP record |

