|  | Influenza vaccination | Electronic GP record |

The absence of any of those characteristics in the database is assumed to indicate no presence of the characteristic under study (missing values are coded absent).

Covariate values are updated on 1^st^ September of each study year on information recorded in the study database.

| Continuous update of co-variates takes place. However, some need to be defined pre-season for analysis. |
| --- |

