**Cohort study**

V/E is calculated as 1- RR, where RR is the attack rate of the vaccinated group over the attack rate of the unvaccinated group.

Multivariable Poisson regression will be used with vaccination and week set as time varying covariates and all other variables set according to the individual’s status as of 1^st^ September 2022 (or 2023).

Adjustment for week of swab, age group, sex, risk-status and region (or practice) and will be included at minimum. Inclusion of additional variables including consultation quartile, IMD quintile, ethnicity, smoking status, influenza vaccination status, EFI, large residence, Cambridge Mortality Measure, will be considered individually; variables that do not impact both hospitalisation or death VE by more than 1% need not be included (i.e. the same adjustments will be made for both death and hospitalisation VE).

Vaccination status will be a time-varying categorical variable: 0-13 days post dose, 14-90 days post dose, 91-182 days post dose, with separate categories for vaccine type (and manufacturer if required). Vaccinated 6months+ ago will be the baseline category, to look at the incremental benefit of a new dose.

Person time will be calculated in days and adjusted for as an offset in the model.

The reshape and collapse commands in Stata will be used to aggregate person time and events across the levels of the time varying and fixed covariates.

Cohort analyses will be carried out for both hospitalisation and death outcomes.

Primary cohort analysis will include complete cases only, but unknown categories may be included for some missing data items.

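### Single occupancy is cited as a reason for the household covariate but has no level in it, so possible confounding by living alone is never tested

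*Protocol*

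**What the plan says.** All references are to the COVID-19 study in the protocol.

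- **Section 3.8, rationale.** Under the heading "Resident in a large household", the covariate is to be built from the household key, and the reason given is: "Single occupancy and large communal establishments have consistently been associated with test positivity and risk of mortality".
- **Section 3.8, grouping.** The only grouping rule is: "We assign to groups based on median age <70, 70+ (e.g. care homes".
- **Section 3.9, Table 1.** The only household item is "Indicator of living in a large residence", sourced from the electronic GP record through the household key. Below the table, the general coding rule is: "The absence of any of those characteristics in the database is assumed to indicate no presence of the characteristic under study".
- **Section 3.12, cohort model.** The candidate adjusters are introduced as: "Inclusion of additional variables including consultation quartile, IMD quintile, ethnicity, smoking status, influenza vaccination status, EFI, large residence, Cambridge Mortality Measure". Each is considered individually and may be left out if it does not move VE by more than 1%.
- **Section 3.12, TND model.** The corresponding list contains "smoking status, EFI, large residence, Cambridge Morality Measure, and indication for swabbing", under a similar 1% rule.

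No section defines, collects or adjusts for single occupancy.

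**The concern.** The protocol gives two household characteristics as its reason for the covariate and carries only one of them forward. Anyone without the large-residence flag falls into the reference level, whether they live alone or share an ordinary home.

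The two outcomes mentioned in that rationale matter to this study. Mortality bears on COVID-19 death, a primary cohort outcome. Test positivity bears on the TND endpoint. If living alone is also related to having had the booster, given the other covariates, then VE carries some residual confounding. The plan's own check would not show it, because that check is applied to the large-residence variable and not to living alone.

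Section 3.2.1 says that data capture covers all relevant potential confounders, and Section 4.5 concedes that healthy-vaccinee behaviour is hard to capture. A household marker that the protocol already cites, and that the household key could supply, deserves the same screening as smoking or deprivation.

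**Working it through.** **Step 1: is single occupancy separated anywhere?** The protocol states no figure to reproduce, so the first check is textual.

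| Place | What it carries |
|---|---|
| 3.8, rationale | Single occupancy and large communal establishments |
| 3.8, heading and grouping | Large household, split by median age at 70 |
| Table 1 | Large-residence indicator |
| 3.12, cohort model | Large residence, optional |
| 3.12, TND model | Large residence, optional |

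A looser reading of the grouping rule does not help. If the median-age split applied to every household, a sole occupant's median age would be their own age. They would be grouped with shared households on the same side of 70, so living alone would still not be separated.

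**Step 2: how much could it matter?** The documents give none of the inputs needed, so everything in this step is assumed and shown as a range.

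- p1 and p0: share living alone in boosted and in comparator person-time. For the TND, these are the shares among vaccinated and comparator controls.
- RR: outcome rate ratio for living alone (for the TND, the odds ratio for positivity).
- Bias factor: B = [1 + p1(RR - 1)] / [1 + p0(RR - 1)].
- Crude VE = 1 - (1 - true VE) × B.

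Example with p1 = 0.25, p0 = 0.35, RR = 1.5 and true VE 60%: B = 1.125 / 1.175 = 0.9574, and VE = 1 - 0.40 × 0.9574 = 61.70%, a shift of +1.70 points.

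Shift in VE, in percentage points, by share living alone (boosted v comparator):

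| True VE | RR | 30% v 30% | 28% v 32% | 25% v 35% | 20% v 35% | 35% v 25% |
|---|---|---|---|---|---|---|
| 30% | 1.2 | 0 | +0.53 | +1.31 | +1.96 | -1.33 |
| 30% | 1.5 | 0 | +1.21 | +2.98 | +4.47 | -3.11 |
| 30% | 2.0 | 0 | +2.12 | +5.19 | +7.78 | -5.60 |
| 60% | 1.2 | 0 | +0.30 | +0.75 | +1.12 | -0.76 |
| 60% | 1.5 | 0 | +0.69 | +1.70 | +2.55 | -1.78 |
| 60% | 2.0 | 0 | +1.21 | +2.96 | +4.44 | -3.20 |
| 90% | 1.2 | 0 | +0.08 | +0.19 | +0.28 | -0.19 |
| 90% | 1.5 | 0 | +0.17 | +0.43 | +0.64 | -0.44 |
| 90% | 2.0 | 0 | +0.30 | +0.74 | +1.11 | -0.80 |

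Reading the plan's 1% rule as one percentage point, some settings pass it and others do not. At a true VE of 90% nearly all stay below it. The shift in points grows as VE falls, which is relevant because Section 3.12 targets the incremental benefit of a new dose over vaccination six or more months ago.

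**Step 3: what the comparator does to the size.** Suppose 30% live alone, with final uptake of 70% in them and 78% in others.

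- Boosted: p1 = (0.30 × 0.70) / (0.30 × 0.70 + 0.70 × 0.78) = 0.21 / 0.756 = 0.278.
- Never boosted: p0 = (0.30 × 0.30) / (0.30 × 0.30 + 0.70 × 0.22) = 0.09 / 0.244 = 0.369. A true VE of 40% reads 41.0% at RR 1.2 and 42.7% at RR 1.6.
- The cohort baseline also includes person-time from people boosted later (Section 3.5). If that equals 25% of their follow-up, p0 = (0.09 + 0.0525) / (0.244 + 0.189) = 0.1425 / 0.433 = 0.329. The same VE then reads 40.6% to 41.5%.

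So a comparison with never-boosted people overstates the shift that the time-varying analysis would show. All these figures are also crude, before adjustment for any other covariate.

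**The case against.** A reader might infer that a known confounder has been left in and that VE will be overstated. The documents do not support that. Confounding needs a link with booster status as well as with outcome, conditional on the other covariates, and no section states one. Section 3.8 says associated without giving a direction. The three sources it cites are 2020 publications, two of them by title on the first wave or peak. Vaccination began in December 2020 (Section 1), so they cannot inform booster uptake. The sign is open, and the shift may be zero.

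It is also fair to say that both models adjust for age group, risk status, week and region or practice at minimum, with frailty, deprivation, consultation and mortality scores as candidates. These could absorb part of any effect of living alone. Passing 1% in a crude calculation does not mean passing it after adjustment. These points stand, and they limit what can be claimed about size.

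Two further objections carry less weight. The candidate lists are worded as open, so nothing forbids testing living alone; but Table 1 names only a large-residence indicator, so a plan followed as written would not have the variable to test. Coding of an optional covariate could be left to a SAP; but the protocol fixes this coding itself in Section 3.8 and Table 1, and that coding omits half of its own rationale. The 1% rule screens on observed change in VE and asks for no prior proof of confounding, so the lack of such proof does not justify leaving this factor out of the screen.

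**Conclusion.** The point holds as an untested gap. The protocol cites single occupancy as consistently associated with positivity and mortality, then merges people living alone with ordinary households in Section 3.8, Table 1 and both models. Possible confounding by living alone is therefore never examined.

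Its size and direction are unknown. Under the assumed inputs the crude shift on a true VE of 60% runs from zero to +4.4 or -3.2 points. It is wider at low VE and mostly under one point at 90%. These figures rest on assumed prevalences and rate ratios, ignore adjustment, and are illustrations only. They should not be read as showing that VE is biased upwards or that the factor would survive the 1% rule. The case for change is that the protocol names the factor, already uses the key that could identify it, and has a screening rule ready to apply.

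**What to change.** Derive a household-type factor from the household key with four levels:

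1. single occupancy;
2. ordinary household (reference);
3. large residence, median age <70;
4. large residence, median age 70+.

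List it in Section 3.8 and in Table 1, so that it is part of the data extract. Enter it as the candidate covariate in place of large residence in the cohort and TND models in Section 3.12, under the existing 1% change-in-VE rule. If it falls below the threshold it can be dropped like any other candidate, and the question will have been tested. If single occupancy is left out on purpose, for example because the key does not identify it reliably, Section 3.8 should say so.

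The cost is one more derived level, with some misclassification where the household key is out of date. The protocol does not say how reliably the key identifies people living alone, so a brief check of that should accompany the derivation.
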